### **4.3 Secondary Objectives**

Secondary objectives are to test dynamic postural control and cervical proprioception in a clinical setting with a simple motor task. The motor task performance of patients with CNLBP will be compared with healthy controls. The motor task for postural control will be to recover normal standing on a labile platform after a slight platform perturbation. The setup measures dynamic control of posture. For cervical proprioception, head repositioning acuity will be measured.

### **4.4 Safety Objectives**

The study's safety objectives are to systematically record any adverse events in order to assess the safety of SMT in the clinical setting.

## **5. STUDY OUTCOMES**

### **5.1 Primary Outcome**

The primary endpoint will be the functional status to assess impairment of daily activities and the self-reported pain after the intervention.

### **5.2 Secondary Outcomes**

Secondary endpoints will be the assessment of the quality of postural control (centre of pressure, platform sway and Uncontrolled Manifold Index (UCM)), and the proprioceptive acuity of cervical repositioning sense (head-repositioning error).

### **5.3 Other Outcomes of Interest**

Therapy documentations will also be analysed qualitatively to compare the amount of active and passive treatments applied during the conventional physiotherapy sessions. Particularly the physiotherapist's patient diagnosis will be extracted to compare with the outcome of postural control. Congruency of prediction could be analysed, i.e. does the dynamic analysis of postural control suggest similar postural deficiencies as described by the therapist?

### **5.4 Safety Outcomes**

A weekly reporting scheme will document progress of the study. Any occurrences will be recorded to the sheet, including adverse events or identified potential risks.

## 6. STUDY DESIGN

### 6.1 General study design and justification of design

The intended procedures and study stages are summarised in Table 1 and Figure 1. Patients will be recruited from the out-patient department of the study site (Reha Rheinfelden) and public advertisement. In a cross-sectional study, baseline (BL) values are recorded to assess and to identify expected discrepancies in postural behaviour in a group-wise comparison (healthy vs. patients with LBP). In a pilot randomised sham-controlled trial (RCT) with parallel groups and blinded assessors, the effects of added SMT to conventional therapy in comparison to added LIT will be evaluated on three additional measurement events. The primary endpoints are pain and function before ( $T_0$ ) and after 9 treatments during 5 weeks (twice a week). Short-term effects will be evaluated within a week after the last training session ( $T_1$ ). Long-term effects will be tested four weeks after the last training session ( $T_2$ ).

*Screening and pre-intervention assessments:* Potential participants will be informed (personal or by phone and email) of the study procedures, risks and expenses, and possible benefits (according to the patient information sheet approved by the competent ethical committee, CEC). After written and oral information, the patient will have one to three days to consider participation before giving informed consent. Once written consent is provided, a baseline measurement will take place 2 to 4 days prior to therapy commencement. For healthy participants there is no time constraint. An internal rheumatologist will confirm the diagnosis for patients who are not referred to the clinic by their treating physicians. The BL assessment will reveal whether all eligibility criteria are fulfilled and whether trial participation is granted. Patients will also be asked to give a second oral consent to further participate in the trial. Once included and randomised for treatment groups, all analysis will follow intention-to-treat principles (as-per-case analysis will also be conducted).  $T_0$  will be conducted immediately before first treatment to ensure a stable baseline (4 to 7 days after BL).

*Interventions and follow-up assessments:* Patient allocation to either the sham- or the experimental PPT group will be block-randomised with a 1:1 allocation ratio. The sequence list will be guarded by the central pharmacy (central randomisation list). Before the first treatment begins, the treating therapist will call the pharmacy to learn the allocated group belonging to the patient's identification number. All patients will receive usual physiotherapy as deemed appropriate by the therapist for 30 minutes. Patients allocated to the CG will subsequently be instructed on how to use the treadmill, stationary bike, or cross-fit trainer at low intensity (Borg 6-9). Patients in EG will receive supervised instructions to use the therapy device (Posturomed®) correctly. For treatments 2 to 9, patients in both groups will not be supervised directly but a trained therapist will be nearby to oversee the compliance and correct execution of the exercise. The therapist will evaluate quality of the execution of exercises after the 3rd and 6th session to instruct increased difficulty if the patient already masters the task. Within one or two days after the 9th treatment, the second assessment ( $T_1$ ) of primary and secondary outcomes will be conducted by the PL or a technical assistant to record possible short-term effects. Finally, four weeks after the last treatment a follow-up measurement will assess long-term effects of the treatments. All measurement events (ME) are expected to take about 60 minutes for all outcome assessments. Total therapy duration is 45 minutes (30 minutes therapy and 15 minutes experimental or sham intervention). The therapist will be blinded to the results of all primary and secondary outcomes. The assessor will remain blinded to group-allocation. For description of the sequence generation and randomisation procedures, please refer to section 6.2.

*Limitations:* The study-protocol features some technical, methodological and physiological limitations that must be considered when interpreting the results. First, the physiological limitation concerns the indirect measure of proprioception which limits the interpretation regarding increased afferent input. Joint repositioning sense only tests one aspect of proprioception on a conscious level. Second, from a methodological point of view, it is not possible to blind the therapist or the patient to the intervention. This may influence the way patients respond to subjective outcomes and could potentially bias the results. Furthermore, in a clinical setting it is not possible to control all co-interventions as treatment must be adapted to the needs and indications of each patient. With multiple therapists at work standardisation of the experimental intervention is adamant. Third, the recording of non-active markers is always related to some inaccuracies. The measurement device records with a resolution that allows accuracy of about 3 mm. This may limit the detectability of the expected change in postural control.

A further methodological limitation is that both assessment for secondary outcomes and the experimental intervention involve the same device (Posturomed). However, the task for the assessment deviates substantially from the training task and no advantage is expected for EG group when performing the postural control task (described in section 9.2.2).

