| Measurements and procedures:    | 
Interested individuals will be informed (written and personally) and given at least 24 hours of consideration time before being invited to baseline (BL) measurements.
 
Healthy participants will be invited for a single baseline measurement of all primary and secondary outcomes.
 
Patients with CNLBP will be invited to baseline measurements after which they may still decide whether or not they would like to take part in the RCT trial. After a second assessment (pre-intervention, T0), included patients will then be randomly allocated to either the experimental (EG) or the control group (CG). All participating patients will receive standard physiotherapy. CG will receive additional exercise therapy (LIT), the EG will receive additional SMT.
 
One or two days after (T1) and four weeks after (FU) the last treatment, the project leader (PL) or the technical assistant will record the post-intervention assessment of the primary and secondary outcomes.
 
Each assessment will consist of a postural control task (standing on a labile platform and stabilising anticipated anterior-posterior sway), a head-repositioning task, and two questionnaires. Total duration will be approximately one hour.
 |

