## 9.2 Assessments of outcomes

### 9.2.1 Assessment of primary outcome

Whilst preparing the setup and software configuration, the subject will be given 10 minutes time to fill in the personal data sheet, including the VAS scales for pain, and the ODI questionnaire for functional status. The questionnaires will be filled in by the patients at every measurement event (BL, T0, T1, and T2).

Self-reported impairment in daily activities will be assessed using the German version of the Oswestry Disability Index (ODI-D), which shows a good reliability. The ODI has ten sections about daily activities (pain, body hygiene, lifting objects, walking, sitting, standing, sleeping, sexual behaviour, social life, and travelling). Each section can be rated from 0 (no pain during activity or pain getting worse) to 5 (I cannot do it myself). The total score is in percentage of the total 50 points, if each section was answered (45, if 9 sections were answered, and so on). The end score will be from 0% (minimal impairment) to 100% (bedridden). A change of 4 points is considered as clinically relevant [26].

Self-reported pain will be assessed using the German version of the Visual Analogue Scale (VAS). It shows a good reliability with a correlation of 0.937 between the first and the second assessment. The VAS is a 100mm line with two endpoints representing the extreme states "no pain" and "pain as bad as it could be". A minimum of 13 mm difference on the scale is considered as clinical relevant [26].

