### 9.2.2 Assessment of secondary outcomes

The secondary outcomes, joint repositioning sense and postural control, will be measured at each measurement event (BL, T0, T1, and T2).

The experimental set-up consists of the neuro-orthopaedic therapy system Posturomed® 202 with handrail (Haider Bioswing, Pullenreuth, Germany), an attached provocation module (Haider Bioswing GmbH, Pullenreuth, Germany), a high-speed camera Basler A602F (Basler AG, Ahrensburg, Germany), a personal computer with Windows 8 operating system to which the camera is attached with USB 3.0, an accelerometer attached to the base-plate of the Posturomed®, and optical markers to measure different joint deflections and joint motion. The markers will be tracked with the motion analysis software Templo (v.7.1.304, Contemplas GmbH, Kempten, Germany). COP is measured by means of a Zebris FDM-S force measuring plate on top of the swaying platform.

After evaluating primary outcomes, the participants will be equipped with markers as shown in Figure 2 below. After familiarisation with the Posturomed's labile surface, he or she will be instructed to adopt an upright posture with the arms folded across the chest (in order to keep hip markers visible). On the cue "ready-steady-go", the assessor will release the platform from its 5 cm deflection. The swaying is recorded until complete damping of the oscillation has occurred (approximately 15

seconds). As participants will be standing on both feet, any facilitation of the task through engaging brakes would make the task too easy (as tested in pre-pilot tests). Hence, all of the device's brakes will be released for this test allowing maximal sway. The camera setup will record the entire task. The task will be repeated five times for each patient. The arithmetic mean of the five trials will be used for further analysis.

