## **11.4 Planned Analyses**

Baseline imbalance between groups will be tested with a student t-test. Differences in means between healthy participants and patients with CNLBP will be analysed with independent student t-tests. A mixed (2) Group x (2) ME ANOVA with repeated measures during ME will be conducted for each dependent variable individually (Pain VAS, Functional Status ODI, Postural Control COM and CM, Proprioception JRE, and Motor Equivalence UCM).

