### **13. PUBLICATION AND DISSEMINATION POLICY**

The project shall eventually result in three to four publications including the findings of the cross-sectional study, a retest analysis and the RCT. Publication of a technical paper on the methodologies will be considered. It is intended to publish in open access journals relevant to the field. Authorship has been negotiated within the steering committee.

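### Each outcome is measured twice before randomisation (BL and T0), but the 2 x 2 ANOVA in 11.4 gives BL no part in the between-arm comparison; an ANCOVA could use both values at almost no cost

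*Protocol*

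**What the plan says.** - **Two pre-treatment measurements.** Protocol 9.2.1 says of pain and ODI: "The questionnaires will be filled in by the patients at every measurement event", listing BL, T0, T1 and T2. Section 9.2.2 says the same of the rest: "The secondary outcomes, joint repositioning sense and postural control, will be measured at each measurement event". Table 1 marks both outcome classes at all four events.
- **Both precede randomisation.** After the T0 assessment, the synopsis says, "included patients will then be randomly allocated to either the experimental (EG) or the control group (CG"). Table 3 also places randomisation after the second visit.
- **Purpose of T0.** Section 6.1 states that T0 "will be conducted immediately before first treatment to ensure a stable baseline (4 to 7 days after BL"). It does not say how stability is judged or how BL enters that judgement.
- **Model.** Section 11.4: "A mixed (2) Group x (2) ME ANOVA with repeated measures during ME will be conducted for each dependent variable individually". No covariate is named. The two events are not named there either, but 6.1 supplies the first: "The primary endpoints are pain and function before" (T0) and after the nine treatments.
- **Stated uses of BL.** It confirms eligibility. In 6.1, "baseline (BL) values are recorded to assess and to identify expected discrepancies in postural behaviour in a group-wise comparison" of healthy people and patients. Section 13 plans papers on "the findings of the cross-sectional study, a retest analysis and the RCT".

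**The concern.** A single questionnaire or a single postural session carries day-to-day error that repetition within the session cannot remove. A second session some days apart can reduce it, and every randomised patient already attends one. A model with two time levels that starts from T0 cannot take that second value in. This is distinct from the choice between ANOVA and ANCOVA, because an ANCOVA on T0 alone would also leave BL out.

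What is at stake is precision. Section 11.2 plans 10 patients per intervention arm, and 11.3 commits to reporting whatever sample is reached. In a trial of that size, a reduction in variance that needs no visit and no patient is worth having, even if it is modest.

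**Working it through.** **The plan's own figure.** Section 11.2 gives 10 per arm at 80% power and alpha 5%. The effect sizes behind it are not in the document, so it cannot be reproduced forward. Solved backward (two-sided, normal approximation), d = sqrt(2 x (1.96 + 0.84)^2 / 10) = 1.25; with the t distribution it is 1.32. The one nearby effect given, 1.4 / 0.19 = 7.4, is not the source of 10.

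**Notation.** Outcome variance is 1 at every visit; r = corr(BL, T0); p = corr(pre, post), taken first as the same for BL and T0. The Group x ME test in a 2 x 2 mixed ANOVA is the t-test on change scores. Variances per patient:

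- change from T0: 2(1 - p)
- ANCOVA on T0: 1 - p^2
- ANCOVA on the BL/T0 mean: 1 - 2p^2/(1 + r)

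**Inputs.** r = 0.937 is the VAS retest correlation in 9.2.1; the interval between those two assessments is not stated. No retest figure is given for the ODI or the secondary outcomes, so r = 0.6 to 0.8 is an assumption, as is p = 0.5 to 0.7 with p not above r.

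**Worked case.** r = 0.937, p = 0.5: ANCOVA on T0 gives 1 - 0.25 = 0.750; ANCOVA on the mean gives 1 - 0.5/1.937 = 0.742, a fall of 1.1%.

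| r | p | Change, T0 | ANCOVA, T0 | ANCOVA, mean | Fall from second baseline | Total fall from change scores |
|---|---|---|---|---|---|---|
| 0.937 | 0.5 | 1.000 | 0.750 | 0.742 | 1.1% | 25.8% |
| 0.937 | 0.7 | 0.600 | 0.510 | 0.494 | 3.1% | 17.7% |
| 0.8 | 0.5 | 1.000 | 0.750 | 0.722 | 3.7% | 27.8% |
| 0.8 | 0.7 | 0.600 | 0.510 | 0.456 | 10.7% | 24.1% |
| 0.7 | 0.5 | 1.000 | 0.750 | 0.706 | 5.9% | 29.4% |
| 0.7 | 0.7 | 0.600 | 0.510 | 0.424 | 17.0% | 29.4% |
| 0.6 | 0.5 | 1.000 | 0.750 | 0.688 | 8.3% | 31.2% |
| 0.6 | 0.6 | 0.800 | 0.640 | 0.550 | 14.1% | 31.2% |

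**In patients.** On a total of 20, the second baseline is worth 20 x 0.750/0.742 = 20.2 to 20 x 0.510/0.494 = 20.6 at r = 0.937, which is less than one patient. Over the assumed range it is worth 20 x 0.750/0.722 = 20.8 to 20 x 0.510/0.424 = 24.1, or about one to four patients.

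**In power.** Suppose the 2 x 2 ANOVA had exactly 80% at 10 per arm. With ANCOVA at 17 degrees of freedom and a variance inflation of 1 + 1/17:

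- r = 0.937: 87.9% on T0 and 88.3% on the mean (p = 0.5); 83.7% and 84.8% (p = 0.7).
- r = 0.7, p = 0.6: 85.8% and 89.2%.

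**If BL tracks the post value less well than T0 does.** Write p0 = corr(T0, post) and pB = corr(BL, post).

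- Using the mean as the pre value in the change-score ANOVA changes the variance by (p0 - pB) - (1 - r)/2. It loses precision once the gap exceeds (1 - r)/2: 0.03 at r = 0.937, 0.10 at 0.8, 0.15 at 0.7.
- ANCOVA on the mean has residual variance 1 - (p0 + pB)^2 / (2(1 + r)). It beats ANCOVA on T0 only if pB exceeds p0(sqrt(2(1 + r)) - 1). At p0 = 0.6 the tolerable gap is 0.019 at r = 0.937 and 0.094 at r = 0.7.
- Example: r = 0.937, p0 = 0.60, pB = 0.55. Change from T0 is 0.800 and change from the mean is 0.819. ANCOVA on T0 is 0.640, on the mean 0.659, and on both values as separate covariates 0.639. ANCOVA on the mean gives back a little against ANCOVA on T0, but stays far below the planned change-score analysis.

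**The case against.** The strongest reply is that nothing here is wrong. Taking the last value before treatment as baseline is standard, and 6.1 does so deliberately, assigning BL to the cross-sectional part and evaluating the trial on three further events. That stands: no bias or contradiction is shown. The point survives only because 11.4 fixes a specific model that leaves BL out of the arm comparison. The synopsis mentions a repeated-measures ANOVA without a number of time levels, but does not give BL a role in that comparison either.

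Three stronger readings are tempting and are not supported:

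- **That BL is collected and thrown away.** It is not. It decides eligibility, feeds the healthy-versus-patient comparison and supplies the retest analysis.
- **That a gain of 10% to 25% is on offer.** Those figures come from putting the BL/T0 mean into the change-score test under assumed BL-T0 correlations of 0.6 to 0.8. The only retest figure in the protocol, 0.937, gives about 3% to 5% on that test.
- **That the mean should simply become the pre value in the existing ANOVA.** This can lose precision, as shown above. BL is also the visit at which entry is decided and the first study exposure to the tasks. Averaging it in would carry practice effects and regression to the mean into the time effect, which is part of the first hypothesis in 11.1.

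The reply that BL may predict the post value less well than T0 also stands in part: it limits the gain from a covariate built on the mean.

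**Conclusion.** The point holds as an efficiency improvement. BL and T0 both precede randomisation, and the planned between-arm model uses only T0. Against ANCOVA on T0 alone, adding BL through the mean is worth about 1% to 3% of residual variance for the VAS at the documented correlation. It is worth about 4% to 17% if r is 0.6 to 0.8 and p is 0.5 to 0.7, which the protocol neither supports nor rules out for the ODI and the secondary outcomes. Both ranges rest on equal variances and on BL and T0 correlating equally with the post value.

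The second baseline may be the smaller part of the benefit: moving from change scores to ANCOVA on T0 alone cuts variance by 15% to 25% for p from 0.7 down to 0.5. A reader might infer that the planned ANOVA is invalid. It is not; under randomisation it compares the arms without bias from this source, only less precisely than the data allow.

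**What to change.** In 11.4, state that the between-arm effect for each outcome is estimated by ANCOVA on the post-treatment value, with the mean of BL and T0 as the pre-randomisation covariate and T0 alone where BL is missing. State also that T0 remains the before value for any within-group change, so that the time effect is not altered.

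If BL is expected to predict the post value clearly less well than T0, for example through learning on the platform task, BL and T0 can be entered as two separate covariates. The choice should be fixed before unblinding.

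The cost is a short addition to 11.4 and one degree of freedom for the covariate (17 instead of 18 with 10 per arm), or two if both values enter separately. No visit, measurement or patient is added, and the other uses of BL are unaffected.

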## **6.2 Methods of minimising bias**

### **6.2.1 Randomisation**

Participants will be randomly assigned to either control or experimental group with a 1:1 allocation as per the computer generated randomisation schedule using permuted blocks of random sizes. The block sizes will not be disclosed, to ensure concealment. A technical assistant otherwise not involved in the study will create the randomisation list, which will be stored in the clinic's pharmacy.

### **6.2.2 Blinding procedures**

The assessor will remain uniformed about group allocation. During the assessment, the participating patients will repeatedly be reminded not to mention treatment group during assessments. The list with sequential participant numbers and randomised allocation will be stored out of sight of the assessor. Concealment will remain after study finalisation for data analysis. Both treatments, control and experimental, will take place in the same room as a measure against the likelihood that the PL would be able to guess group allocation when accidentally seeing the participant in the corridors.

### **6.2.3 Other methods of minimising bias**

The questionnaires for pain and functional status are all standardised and self-ministered.

Prior to study commencement, the involved therapists will attend a standardisation training where the exact execution and documentation of the intervention is trained. This will also entail standardisation of conventional treatment to the extent of possibilities within therapeutic practicability.

## **6.3 Unblinding Procedures (Code break)**

The PL and assessors will never be unblinded to the patient allocation as they are otherwise not involved treatment of the patients. As therapists and medical staff are not blinded from the first place, there is no protocol for unblinding procedures.

[figure not shown]

**Figure 1: Study procedure flow-chart**

## 7. STUDY POPULATION

### 7.1 Eligibility criteria

Participants fulfilling all of the following inclusion criteria are eligible for the study:

- Patients with musculoskeletal low back pain (lumbosacral pain, with or without radicular pain).
- Pain and discomfort localized below the costal margin and above the inferior gluteal folds, with or without referred leg pain of at least 3 months' duration.
- Currently seeking care for low back pain.
- Age above 18 years.
- Comprehend German.
- Informed Consent as documented by signature (Appendix Informed Consent Form).

The presence of any one of the following exclusion criteria will lead to exclusion of the participant:

- Clinical signs of neurological damage (i.e. paresis or tingling in limbs).
- Traumatic injury to the musculoskeletal system, such as fractures or tumours.
- Suspected or confirmed spinal pathology (e.g., tumour, infection, fracture, and inflammatory disease).
- Previous spinal surgery.
- Major surgery scheduled during treatment or follow.
- Pain in the neck or cervical spine that reduces active movement to less than 30° rotation to each side
- Whiplash during the last year
- Known vestibular pathologies
- Inability to follow the procedures of the study, e.g. due to language problems, psychological disorders, dementia, etc. of the participant.
- Parallel participation in another study.
- Previous enrolment into the current study.
- Enrolment of the investigator, his/her family members, employees and other dependent persons.

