| Inclusion / Exclusion criteria: | 
Inclusion criteria:
 
 
• Patients with clinically confirmed musculoskeletal low back pain (non-specific low back pain)
 
• VAS pain > 0; ODI>0
 
• Age ≥ 18 years
 
 
Exclusion criteria:
 
 
• Known or suspected neurological diseases or lesions
 
• Traumatic injury of musculoskeletal system (fractures, tumours)
 
• Spinal pathologies (e.g., tumour, infection, fracture, and inflammatory disease)
 
• Previous spinal surgery
 
• Presence of any contraindication to exercise (fracture or cardiovascular limitations)
 
• Pain in the neck or cervical spine that reduces active movement to less than 30° rotation to each side
 
• Whiplash during the last year
 
• Known vestibular pathologies
 
 
Healthy group:
 
Participants of the healthy group must be free of neurological or orthopaedic limitations to daily activity (VAS=0; ODI=0).
                                                                                                                                                                                                                      |

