### **3.7 Risks/Benefits**

The exercises on the labile platform are rated as “absolutely safe” by the developer. Ever since the therapy has been implemented (1993), no adverse events have been reported during or after training on the device. The labile surface may trigger some fear of falling, but the railings that surround the device allow control of stability at any time. Nevertheless, it is not recommended to use the device during acute phases of intense pain or inflammation of weight bearing joints (e.g. knee or hip joints). Also, severe vestibular deficits or M. Menière may also lead to inability to stand stable and securely on the platform. To mitigate these risks, eligibility criteria will exclude participants with any risk-bearing contra-indications.

Although not confirmed systematically, the benefits expected outweigh the minimal risks by far. It is expected that an overall improvement of balance and postural control improves reactivity and reduces risk of falling in daily activity. Specific improvement of inter-vertebral musculature and improvement of the fine-tuned control of posture is believed to relax tensed poly-segmental muscles and decrease long-term strains and pain.

Patients that are enrolled into the study are covered by indemnity for non-negligent harm associated with the protocol through the clinic's own insurance (National Suisse, police-nr: 40.025.077). This will cover compensation or damages whether awarded voluntarily by the Sponsor, or by claims pursued through the courts. Incidences judged to arise from negligence (including those due to major protocol violations) will not be covered by study insurance policies.

If patients feel they benefited from the additional PPT therapy, additional training sessions can be organised for the patient. However, this will be outside of the study and will require either a new referral from the treating physician or the costs must be beard by the patient him- or herself.

Irrespective of treatment success, the study shall produce new insight into the understanding of the mechanisms behind human postural control and its relation to musculoskeletal pain.

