**Figure 2: Marker configuration for video-based postural control assessment**

An additional setup is installed to measure cervical proprioception (Figure 3). On a wall facing a chair, there are vertical lines that represent the 30° and 60° angle to the left and the right side. Participants are blindfolded to avoid opening of the eyes and visual input during testing. Additionally, they wear a headgear to prevent acoustical input like computer ventilation (instructions are still perceptible). A laser pointer is fixed on the headgear. A computer mouse fixed to the hand side of the participant can be clicked to indicate when the head position is perceived to be at the instructed angle. Each click records the exact time and allows post-measurement synchronisation with the motion-tracking data. Cameras stand both lateral and posterior to the participant. The lateral camera records any possible deviations in posture of the trunk during measurements.

The testing order is randomized. The instructor gives cues following the test protocol. Five trials are used because more than three repetitions seem to be needed in order to reduce variability of the results but less than ten to avoid fatigue and noncompliance of Participants. Participants hold the laser pointer on the target angle line for 15 s (with one click on the left mouse-button for data of reference position). After returning to neutral position, participants replicate the target angle position followed by a mouse-click to confirm position. This procedure is repeated five times for one target angle before proceeding to the next angle. To measure repositioning of neutral position, participants hold in their personal, most natural way of NP and click the mouse. After holding NP for 15s, they perform a full right and left rotation of the head, directly return to NP and click the mouse.

[figure not shown]

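### The eligibility list in 7.1 does not match the synopsis, 3.7 or the stated population, and its 30° neck-rotation limit admits patients who cannot reach the 60° head-repositioning target

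*Protocol*

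**What the plan says.** **Eligibility.** Section 7.1 states that a participant must meet all its inclusion criteria and that any one of its exclusion criteria leads to exclusion, so it reads as the deciding list. The synopsis gives a second list, which also excludes "Presence of any contraindication to exercise (fracture or cardiovascular limitations", requires VAS and ODI above 0, and describes the population as "Patients with clinically confirmed musculoskeletal low back pain (non-specific low back pain". Section 7.1 instead admits "Patients with musculoskeletal low back pain (lumbosacral pain, with or without radicular pain", and 7.2 likewise includes radicular pain in the diagnosis that the rheumatologist confirms. Section 3.7 names situations in which the device is not recommended or not safe to stand on, and states that "eligibility criteria will exclude participants with any risk-bearing contra-indications".

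**Neck rotation.** The synopsis and 7.1 carry the same exclusion: "Pain in the neck or cervical spine that reduces active movement to less than 30° rotation to each side". For the head-repositioning test, 9.2.2 says that on the wall facing the participant "there are vertical lines that represent the 30° and 60° angle to the left and the right side". It continues: "Participants hold the laser pointer on the target angle line for 15 s". The participant then returns to neutral and reproduces the angle, and "This procedure is repeated five times for one target angle before proceeding to the next angle". A separate neutral-position task follows.

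**The concern.** There are two distinct problems.

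First, someone screening from 7.1 alone could enrol a person whom the synopsis excludes. Section 3.7 presents eligibility as its means of risk mitigation, but the deciding list does not carry all the items that 3.7 needs. The population to which the results apply is also described in two ways.

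Second, the neck-rotation limit is lower than the range the test demands. Some eligible patients cannot be measured at 60° as 9.2.2 describes. Head-repositioning error is the secondary outcome behind the third hypothesis in 11.1 (patients versus healthy controls), and proprioception is also among the variables in the group-by-time analysis in 11.4. The protocol has no rule for a participant who cannot reach a target.

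**Working it through.** No sample size, power or error rate is involved. The check is a comparison of text and of two angles.

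**Step 1: eligibility items side by side.**

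| Item | Synopsis | 3.7 | 7.1 |
|---|---|---|---|
| Contraindication to exercise, including cardiovascular limitation | Excluded | Any risk-bearing contraindication to be removed by eligibility | No such item (fracture is covered, as injury or spinal pathology) |
| Acute intense pain; inflamed weight-bearing joints | Not named, though the wording on any contraindication could cover them | Device not recommended | Not named |
| Vestibular disease | Excluded | Named as a risk | Excluded |
| VAS and ODI above 0 | Required | Not mentioned | Not required |
| Type of back pain | Non-specific | Not mentioned | With or without radicular pain (7.2 agrees with 7.1) |

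Of the conditions that 3.7 names, 7.1 therefore carries only the vestibular one. The primary objective in 4.2 is worded for chronic non-specific pain, as in the synopsis.

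**Step 2: admitted range against required range.**

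- Admitted by both lists: active rotation of 30° or more.
- Required by 9.2.2: reaching and holding a line at 30° and at 60°, left and right.
- Gap: 30° to 59°. A patient in this band is eligible but cannot hold the 60° line on the limited side.

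**Step 3: how much of the test is affected.** There are 2 angles × 2 sides = 4 angular tasks, plus 1 neutral task, which makes 5. A one-sided limit removes 1 of 5 tasks and a two-sided limit removes 2 of 5. At five repetitions per angle, that is 5 or 10 of the 4 × 5 = 20 angular trials. The neutral and 30° tasks remain measurable.

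**Step 4: can the missing-data rule help?** Section 11.5 carries the last observation forward. The patient-versus-healthy comparison uses baseline, the first measurement, so there is no earlier value to carry. At T0, only a baseline value could be carried, and that would be absent too if the restriction was already present.

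**Step 5: share of the data per patient.** At the minimum of 10 patients per arm, one affected patient is 1/20 = 5% of the patient data at the affected target; with 30 patients it is 1/30 = 3.3%. This is the weight of one patient, not an estimate of how many there are. The documents give no distribution of neck rotation.

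**The case against.** The best reply is that 7.1 does not stand alone. Section 2.7 allows exclusion from the intervention after T0 if the baseline measurements contraindicate treatment. Table 3 includes a medical examination in the first eligibility visit. Sections 6.1 and 7.2 require either a physician's referral or confirmation of the diagnosis by the clinic's rheumatologist, and 7.4 ends a session on signs of trouble. It would therefore go too far to infer that unsuitable patients will in fact be treated. These safeguards soften the conflict but do not remove it: 2.7 speaks only of a possibility and gives no criteria, and 7.1 still lacks items that 3.7 assumes are there.

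Other objections also have force:

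- The conditions in 3.7 cannot be said to be absent from both lists, because the synopsis wording on any contraindication may include an inflamed joint. The clear gap is in 7.1.
- The VAS/ODI item matters little in practice. Patients under 7.1 have at least three months of pain and are seeking care, so a score of exactly 0 would be unusual.
- Admitting radicular pain while excluding paresis or tingling is not a contradiction; it can mean leg pain without neurological signs. What remains is the difference between the radicular and non-specific labels.
- Pain-limited rotation can change over the roughly nine weeks of the study, so an affected patient need not fail the 60° trials at every visit.

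The exclusion for inability to follow study procedures might be stretched to cover neck restriction. Its examples are language and mental state, however, and a specific 30° limit stands beside it, so it does not settle the matter.

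**Conclusion.** The point holds on both counts, as inconsistencies that should be corrected. Section 7.1 omits the synopsis exclusion for exercise contraindications although 3.7 depends on eligibility to remove them; the VAS/ODI and radicular-pain differences are real but lesser. The rotation limit and the 60° target do not fit together, which leaves one or two of five head-repositioning tasks unmeasurable in any eligible patient limited to 30-59°.

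A reader might infer that the test of the third hypothesis is biased. The documents do not support that. They give no count of affected patients (it could be zero) and no direction of effect, and they do not say that the 60° trials are pooled into the analysed variable. What can be said is that any such loss would probably fall mainly on the patients, since the synopsis requires healthy participants to be free of orthopaedic limitations to daily activity.

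The primary VAS and ODI analyses and the sample size are not affected by the rotation problem. The conclusion assumes that 7.1 is the list applied at screening and that the 60° lines are used for every participant, as 9.2.2 reads.

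**What to change.** 1. Reconcile the synopsis, 3.7, 7.1 and 7.2 into one eligibility list, identical wherever it appears. It should settle exercise contraindications, the conditions named in 3.7, VAS and ODI above 0, and radicular versus non-specific pain. Which clinical limits apply is for the sponsor to decide.
2. Define the head-repositioning endpoint, for both the patient-versus-healthy and the treatment comparison, on the neutral and 30° targets. Report the 60° results as supplementary, with the number of participants who could not reach the line.
3. State whether the phrase on rotation to each side means a limit on either side or on both. If both sides must be limited, a patient below 30° on one side is admitted and cannot reach that 30° target, so step 2 would need a rule for that case.

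The cost is protocol wording, ethics committee approval if the eligibility change counts as substantial under 2.10, and a slightly narrower secondary endpoint. The measurements need not change, since the 60° trials can still be recorded.
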